### 5.3.2 Randomized comparisons

#### 5.3.2.1 Incidence of hyperkalemia

Only participants without hyperkalemia at baseline will be included in the study. A generalized linear mixed model accounting for clustering will be used for incidence of hyperkalemia

- 1) To evaluate the effect of SS or SSSC alone, the model will be:

The model will include intervention status as fixed effects, as well as cluster as random effects. Thus, the model would be:

$$\begin{aligned} \text{Logit}(P(y_{ij} = 1)) &= \beta_0 + \mu_j + \beta_1 x_{ij} + e_{ij} \\ e_{ij} &\sim N(0, \sigma_e^2) \\ \mu_j &\sim N(0, \sigma_{\mu_j}^2) \end{aligned}$$

Where  $i$  represents the  $i^{\text{th}}$  subjects,  $j$  represents the  $j^{\text{th}}$  cluster (facility),  $y_{ij}$  is the probability of hyperkalemia for subject  $i$  in cluster  $j$ ;  $\beta_0$  is the mean outcome in the control group;  $\mu_j$  is a cluster random effect to allow for between-cluster heterogeneity;  $x_{ij}$ , the predictor of interest, either SS or SSSC, is an indicator of the intervention for subject  $i$  in cluster  $j$  (1 indicates receive intervention while 0 indicates not receive intervention),  $\beta_1$ , the coefficient of interest, is the effect coefficient of intervention;  $e_{ij}$  is the random error for the measurement of subject  $i$  in cluster  $j$ .

2) To test the interaction effect of SS and SSSC, the model will be:

The model will include intervention status as fixed effects, as well as cluster as random effects. Thus, the model would be:

$$\begin{aligned} \text{Logit}(P(y_{ij} = 1)) &= \beta_0 + \mu_j + \beta_1 x_{1ij} + \beta_2 x_{2ij} + \beta_3 x_{1ij} * x_{2ij} + e_{ij} \\ e_{ij} &\sim N(0, \sigma_e^2) \\ \mu_j &\sim N(0, \sigma_{\mu_j}^2) \end{aligned}$$

Where  $i$  represents the  $i^{\text{th}}$  subjects,  $j$  represents the  $j^{\text{th}}$  cluster (facility),  $y_{ij}$  is the probability of hyperkalemia for subject  $i$  in cluster  $j$ ;  $\beta_0$  is the mean outcome in the control group;  $\mu_j$  is a cluster random effect to allow for between-cluster heterogeneity;  $x_{1ij}$  is an indicator of the SS for subject  $i$  in cluster  $j$  (1 indicates receive intervention while 0 indicates not receive intervention),  $\beta_1$  is the effect coefficient of intervention;  $x_{2ij}$  is an indicator of the SSSC for subject  $i$  in cluster  $j$  (1 indicates receive intervention while 0 indicates not receive intervention),  $\beta_2$  is the effect coefficient of intervention;  $\beta_3$  is the coefficient for interaction between SS and SSSC;  $e_{ij}$  is the random error for the measurement of subject  $i$  in cluster  $j$ .

Secondary analysis, with adjustment for unhealthy conditions [2] included hypertension, diabetes mellitus, coronary heart disease, stroke, chronic kidney disease, cancer, chronic obstructive pulmonary disease, being bedridden, or eGFR < 60 mL/min/1.73m^2 will be conducted for both aims above.

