## **2.3 Outcome definitions**

The primary outcome for the study is SBP assessed as continuous variable (in mmHg) evaluated during 24-month follow-up.

Secondary outcomes:

- 1) DBP assessed as continuous variable (in mmHg) evaluated during 24-month follow-up.
- 2) 24-hour urinary sodium (in mmol/d), potassium (in mmol/d), and microalbumin excretion (In mg/d) assessed as continuous variable evaluated during 24-month follow-up.
- 3) Incidence of hyperkalemia. A new case of hyperkalemia is defined as having serum potassium  $>5.5$  mmol/L at either month 12 or 24 among participants with normal serum potassium at the baseline, regardless of clinical manifestations.
- 4) the risk of developing all-cause mortality, cardiovascular events (fatal and nonfatal stroke, fatal and nonfatal myocardial infarction, hospitalization or death caused by congestive heart failure)
- 5) ED-5Q during 24-month follow-up.

- 6) Incidence of renal dysfunction: A new case of renal dysfunction is defined as having eGFR <60 at either 12 or 24 months with normal eGFR at the baseline, regardless of clinical manifestations.
- 7) Incidence of hyponatremia: A new case of hyponatremia is defined as having serum sodium <135 mmol/L at either 12 or 24 months with normal serum sodium at the baseline, regardless of clinical manifestations.
- 8) A cost-effectiveness measure will be estimated based on the incremental cost of achieving each 1-mm Hg reduction in SBP

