**Safety set (SAS):**

SAS will consist of all randomized subjects who: 1) have baseline serum potassium measured 2) have received at least one month of study intervention, regardless of their eligibility. Subject will be analyzed according to the intervention they actually received.

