### 5.3.2.2 incidence of renal dysfunction

Analysis of incidence of renal dysfunction will follow the same approaches as that for incidence of hyperkalemia.

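### The main models for new hyperkalemia, renal dysfunction and hyponatremia leave out the continuous baseline value of the outcome's own laboratory test, at a modest cost in power and precision

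*Supplement*

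**What the plan says.** **Main models.** SAP 5.3.2.1 specifies a logistic mixed model for new hyperkalemia: "The model will include intervention status as fixed effects, as well as cluster as random effects". The model for the SS by SSSC interaction adds the second indicator and the product term, and nothing else. SAP 5.3.2.2 states: "Analysis of incidence of renal dysfunction will follow the same approaches as that for incidence of hyperkalemia". The same sentence stands under 5.3.2.3, the hyponatremia heading. I read the outcome named there as a slip and take the approach to apply to hyponatremia too.

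**Who is analysed.** The safety set in SAP 3.3 is limited to residents who "have baseline serum potassium measured". SAP 2.3 counts new hyperkalemia "among participants with normal serum potassium at the baseline", new renal dysfunction as "having eGFR <60 at either 12 or 24 months with normal eGFR at the baseline", and new hyponatremia as a low sodium "at either 12 or 24 months with normal serum sodium at the baseline".

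**Adjustment elsewhere.** The primary SBP model (SAP 5.1.1) has baseline SBP as a fixed effect. SAP 5.3.2.4 sends mean serum potassium and sodium to that same approach. For the binary safety outcomes, 5.3.2.1 plans a "Secondary analysis, with adjustment for unhealthy conditions". The list covers disease history, being bedridden and eGFR below 60, and Table 7 is the shell for the results. Protocol section 9 (Safety Evaluation) mentions control of confounding but names no covariate.

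**The concern.** Hyperkalemia is the protocol's main safety index (Protocol 6.2), and neither document states power for any safety outcome. If events are few, precision matters, and a missed potassium harm would be the costly error.

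The SAP treats one assay in two ways. Mean potassium is compared with its baseline value in the model, while the proportion crossing 5.5 mmol/L is compared without it. SAP 5.9, which lists and justifies departures from the protocol, gives no reason.

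The covariate is already there. A resident cannot be classed as at risk without it, so adding it loses nobody and needs no imputation. Without it, predictable variation between residents stays in the error, and any chance difference in baseline between 24 and 24 facilities passes into the odds ratio.

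**Working it through.** **1. Is the value available, and is it used?**

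| Outcome | Baseline value needed to be at risk | In main model | In secondary adjustment |
|---|---|---|---|
| Hyperkalemia | potassium (SAP 2.3; also safety set) | no | no |
| Renal dysfunction | eGFR (SAP 2.3) | no | only as below 60, yes/no |
| Hyponatremia | sodium (SAP 2.3) | no | no |

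For renal dysfunction, if normal eGFR means at least 60, everyone at risk has the same value of the eGFR-below-60 term, so it adjusts for nothing.

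**2. The plan's own figure.** There is none to reproduce. The stated power concerns SBP only. I take from Protocol section 10 and SAP 2.4 only the 48 facilities, the 16 evaluable residents in each, the ICC of 0.02 (given for SBP) and the 24 v 24 split per factor.

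**3. Chance imbalance.** In baseline SD units, the SD of the difference in baseline means is

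sqrt(2 × [1 + (m − 1) × ICC] / (24 × m)).

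With m = 16 and ICC 0.02: sqrt(2 × 1.30 / 384) = 0.082. The range is 0.065 to 0.114 for m of 16 to 20 and ICC of 0 to 0.1. In the simulations of step 4, an imbalance of 1.96 of these SDs multiplied the unadjusted odds ratio by 1.07 to 1.21 at correlations of 0.3 to 0.5, and by 1.17 to 1.40 at 0.7 to 0.85.

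**4. Power at ICC 0.02, with assumed event rates.** There were 1,500 simulated trials per setting, with residents abnormal at baseline removed. The analysis was logistic regression with facility-robust standard errors and a t reference, standing in for the SAP's random-intercept model. Entries are power without → with the continuous baseline value.

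| Assumed rates | corr. 0.3 | 0.5 | 0.7 | 0.85 |
|---|---|---|---|---|
| 2% v 5% | 58 → 60% | 58 → 60% | 60 → 66% | 59 → 73% |
| 3% v 8% | 82 → 85% | 83 → 86% | 83 → 90% | 83 → 95% |
| 5% v 11% | 82 → 83% | 80 → 84% | 83 → 88% | 82 → 94% |
| 12% v 20% | 76 → 77% | 77 → 79% | 76 → 84% | 77 → 90% |

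Type I error ran from 3.4% to 6.1% over both models. The Monte Carlo standard error of one power figure is at most sqrt(0.25/1500) = 1.3 points. The two models were fitted to the same simulated trials, so the differences are steadier than that. A gain of 1 or 2 points still means small rather than exact.

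**5. Power on the potassium scale.** Assumptions: baseline mean 4.55 and SD 0.45 mmol/L, two follow-up values, an event if either exceeds 5.5, and a true SS rise of 0.15 / 0.20 mmol/L, with 1,000 trials per setting.

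| Facility ICC | Correlation | Rise 0.15 | Rise 0.20 |
|---|---|---|---|
| 0.02 | 0.3 | 60 → 61% | 86 → 88% |
| 0.02 | 0.5 | 56 → 61% | 82 → 87% |
| 0.05 | 0.5 | 53 → 60% | 80 → 87% |
| 0.05 | 0.7 | 51 → 63% | 80 → 89% |
| 0.15 | 0.5 | 44 → 53% | 69 → 83% |

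A separate run of 1,500 trials at ICC 0.02 and a rise of 0.15 gave 58 → 60%, 57 → 62% and 52 → 61% at correlations of 0.3, 0.5 and 0.7.

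**The case against.** **A baseline-adjusted potassium analysis is already planned.** SAP 5.3.2.4 tests mean potassium on the continuous scale with the baseline value in the model, so a general rise would be examined efficiently. This stands, and it weakens any claim that the plan is blind to potassium harm. It does not answer the question about incidence, which is the named main safety index.

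**An adjusted safety analysis exists.** A reader of the main models alone might infer that the plan adjusts no safety comparison for any baseline laboratory value. The secondary analysis and Table 7 contradict that, since eGFR below 60 is included. What is absent is the analyte's own continuous value.

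**Baseline is partly conditioned on already.** Restriction to residents normal at baseline removes the extremes. That is true, and the simulations include it. Variation within the normal range remains.

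**The size rests on assumptions.** The documents give no mean, SD, ICC or correlation for potassium, eGFR or sodium. The larger gains need a correlation of about 0.7 or more, or a facility ICC above the plan's only stated value. This stands and limits the claim.

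**Chance imbalance is not bias.** A reader might infer that the unadjusted comparison is invalid. It is not: randomisation covers chance imbalance, and type I error stayed near 5%. An imbalance of 0.05 mmol/L with a slope of about 3 log-odds per mmol/L (found at correlation 0.5) shifts the log odds ratio by 0.15, against a standard error of about 0.40. That is under 0.4 of a standard error and lies within the reported interval.

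**Adding the value to the secondary analysis would do.** It would help, but the more precise estimate would then sit in a supporting table.

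**Conclusion.** The concern holds as a cheap improvement in efficiency, not as an error. The three main binary safety models omit a covariate that every at-risk resident has and whose counterpart the SAP uses in its SBP and mean serum electrolyte models. The planned secondary adjustment does not fill the gap.

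At ICC 0.02 the cost is about 1 to 5 points of power at correlations of 0.3 to 0.5 and about 5 to 10 points at 0.7. It is more only at higher correlation (11 to 14 points at 0.85) or higher facility ICC (9 to 14 points at ICC 0.15 and correlation 0.5). All event rates, laboratory distributions and correlations are assumed, and the SBP ICC is borrowed. The simulations used robust-error logistic regression rather than the SAP's mixed model.

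It is tempting to conclude that the plan would miss a true potassium harm. The documents do not support that: the loss may be only a point or two, and the continuous potassium analysis stands beside it.

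**What to change.** Add one prespecified continuous fixed effect to each main model, including the interaction models:

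- SAP 5.3.2.1: baseline serum potassium.
- SAP 5.3.2.2: baseline eGFR.
- SAP 5.3.2.3: baseline serum sodium where measured. Sodium is in the SAP's baseline table shell but not in the laboratory list of Protocol 5.2, so its availability should be confirmed. The outcome name under this heading should also be corrected.

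Report these as the main results and keep the present models as supportive. Limit the covariates to that one value, since events may be few.

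The odds ratio becomes conditional on baseline, so also report a standardised risk difference with an interval that respects clustering. The same standardised risks can fill the relative-risk columns of Tables 6 and 7, which a logit model does not give directly.

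The cost is a few lines of SAP text and one parameter per model. There is no new data collection and no resident is lost. In no setting run did the adjusted model lose power.

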### 5.3.2.2 incidence of renal dysfunction

Analysis of incidence of renal dysfunction will follow the same approaches as that for incidence of hyperkalemia.

#### **5.3.2.3 incidence of hyponatremia**

Analysis of incidence of renal dysfunction will follow the same approaches as that for incidence of hyperkalemia.

#### **5.3.2.4 Serum potassium and sodium**

Both descriptive and model analyses will follow the same approaches as that for the efficacy analyses for primary outcome.

These results will be reported in **Table 6** and **Table 7**

#### **5.3.3 safety monitoring data**

A monitoring plan was conducted in participants allocated to salt substitute to detect possible hyperkalemia due to the use of salt substitute. This includes additional assessment of serum potassium and self-reported questionnaires regarding symptoms of hyperkalemia and medication use at 3- and 6- month. All salt substitute recipients are required to have at least 1 blood assay within 6 months of starting intervention.

Thus, the analysis of safety monitoring data will be performed only on safety dataset in SS group. The data includes serum potassium tests and hyperkalemia questionnaire at month 3, month 6 in SS group.

Below variables will be analyzed:

- 1) incidence of hyperkalemia.
- 2) Serum potassium
- 3) incidence of positive result for hyperkalemia questionnaire

We will list the number of participants with hyperkalemia identified by the monitoring plan in each screening and the results of re-test of serum potassium. We will particularly focus on the trend with time in the number of patients with occasional and persistent abnormal serum potassium.

#### 5.4 Cost-effective analysis

This analysis will be performed in FAS set. A cost-effectiveness measure will be estimated based on the incremental cost of achieving each 1–mm Hg reduction in SBP. The cost is the fee (unit: Yuan )associated with intervention, including cost for salt substitute, faculty training, health education, diagnose and treatment for hyperkalemia. Incremental cost-effective ratio (ICER) will be calculated as below:

$$IC = \text{Cost}_{\text{initial}} - \text{Cost}_{\text{complete}}$$

$$IE = \text{SBP}_{\text{initial}} - \text{SBP}_{\text{complete}}$$

$$\text{ICER} = IC/IE$$

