**Cost-effective analysis:**

A cost-effectiveness measure will be estimated based on the incremental cost of achieving each 1-mm Hg reduction in SBP. The cost is the fee (unit: Yuan )associated with intervention, including cost for salt substitute, faculty training, health education, diagnose and treatment for hyperkalemia. Incremental cost-effective ratio (ICER) will be calculated as below:

$$IC = \text{Cost initial} - \text{Cost complete}$$

$$IE = \text{SBP initial} - \text{SBP complete}$$

$$ICER = IC/IE$$

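### The written ICER formula reverses the sign of cost and names no comparator, so it does not give the incremental cost per mmHg that the plan promises

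*Supplement*

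**What the plan says.** SAP 2.3 lists the economic measure as the eighth secondary outcome: "A cost-effectiveness measure will be estimated based on the incremental cost of achieving each 1-mm Hg reduction in SBP". SAP 5.4 repeats that target and introduces the calculation with "Incremental cost-effective ratio (ICER) will be calculated as below". It then sets out "IC = \text{Cost}_{\text{initial}} - \text{Cost}_{\text{complete" for cost, "IE = \text{SBP}_{\text{initial}} - \text{SBP}_{\text{complete" for effect, and the ICER as the first divided by the second. In plain notation:

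- IC = Cost(initial) - Cost(complete)
- IE = SBP(initial) - SBP(complete)
- ICER = IC / IE

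The costs are fees attached to the intervention, "including cost for salt substitute, faculty training, health education, diagnose and treatment for hyperkalemia". On the population, the SAP says only "This analysis will be performed in FAS set". Protocol V1.4 section 9 has the same three lines, and SAP 5.9, which lists departures from the protocol, leaves them unchanged. Neither document defines initial or complete, attaches a trial arm to any term, or names the comparator for this analysis.

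**The concern.** An incremental ratio compares two strategies: extra cost over extra effect. The trial has natural comparators (SAP 2.1: salt substitute against regular salt, and stepwise supply control against no reduction in supply), but the formula uses neither.

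Two separate faults follow. First, cost is subtracted in the wrong direction for a strategy that adds cost, while the effect term is positive when SBP falls. Second, if initial and complete mean the start and end of the intervention, the ratio describes change over time within whichever group it is applied to. Anything that control homes share is then charged or credited to the intervention. Under protocol V1.4 section 5.4, item 1, control homes also receive general salt-reduction education, and health education is one of the listed cost items.

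Cost-effectiveness is in the protocol title and is a stated secondary aim (SAP 1.2). An analyst who followed the text would report a ratio that could be taken to show savings where there were none.

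**Working it through.** The documents give no numerical ICER, so there is no planned figure to reproduce. The check is algebra plus an illustration.

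**Inputs from the documents.** Net SBP effect of salt substitute 3.0 mmHg and of stepwise supply control 4.0 mmHg (protocol V1.4 section 10).

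**Assumptions, not in the documents.** Intervention cost 100 Yuan per participant (range 50 to 200); control cost 0 or 20 Yuan; control-arm SBP change from a 2 mmHg fall to a 4 mmHg rise.

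**Step 1: sign, start/end reading.** The listed fees accrue once the intervention is under way. With an initial cost of about 0 and a final cost of C, IC = 0 - C, which is negative. If SBP falls, IE is positive. A cost of 100 Yuan and a fall of 3 mmHg give -100/3 = -33.3.

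**Step 2: sign, most charitable reading.** Let initial mean control and complete mean intervention. With costs of 20 and 100 Yuan and a 3 mmHg difference, the ratio is (20 - 100)/3 = -26.7. This is a between-group ratio, but the added cost still appears as a saving. The correct value is (100 - 20)/3 = +26.7.

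**Step 3: missing comparator, start/end reading.** Take a net effect of 3 mmHg, cost 100 Yuan and control cost 0. If control SBP falls by s, the intervention arm falls by 3 + s, and the formula gives -100/(3 + s). The between-group ratio is (100 - 0)/3 = +33.3 whatever s is.

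| Control-arm SBP | IE as written | Formula as written | Cost sign swapped only | Between-group ratio |
|---|---|---|---|---|
| falls 2 mmHg | 3 + 2 = 5 | -20.0 | 20.0 | +33.3 |
| unchanged | 3 | -33.3 | 33.3 | +33.3 |
| rises 2 mmHg | 3 - 2 = 1 | -100 | 100 | +33.3 |
| rises 4 mmHg | 3 - 4 = -1 | +100 | -100 | +33.3 |

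Swapping the cost sign alone does not restore the right value, so the missing comparator is a second fault. The error in size runs both ways. Results scale with cost: at 50 and 200 Yuan the between-group ratio is 16.7 and 66.7. For the 4 mmHg effect at 100 Yuan it is 25.0, against -16.7, -25.0 and -50.0 from the formula in the first three scenarios.

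**Step 4: control cost.** If control homes cost 20 Yuan and control SBP is flat, the formula still gives -100/3 = -33.3, while the between-group ratio is 80/3 = +26.7. Even with no SBP change in control, the size is right only if control cost is negligible.

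**Step 5: the control arm itself.** A cost of 20 Yuan and a 2 mmHg fall give (0 - 20)/2 = -10, although nothing is incremental there.

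**The case against.** The best defence is that the before-after reading is an inference. The labels are undefined, the stated target is an incremental cost, SAP 2.6 says the secondary aims test for difference, and the full-analysis set contains all arms as randomised. The authors may well have intended a between-group ratio. That stands as a limit on certainty about the second fault. It does not supply a comparator, start and end remain the ordinary meaning of the words, and the sign fails on either reading.

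A reader might also infer that the plan must understate the cost per mmHg by some fixed factor, or that the ratio is bound to be wrong in size as well as sign. The documents support neither. They give no control-arm change and no costs; the size error can go in either direction, and it vanishes if control SBP is flat and control cost is nil.

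Nor do the documents make much of regression to the mean or season as sources of shared change. Eligibility has no blood-pressure threshold, and month 24 falls in the same season as baseline. The documented shared element is the health education given to every home.

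Finally, this is one secondary outcome. SAP 2.8 describes the first main report as efficacy and safety, SAP section 6 has no cost-effectiveness table, and no data are lost through the wording. That bears on priority, not on whether the formula is right.

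**Conclusion.** The formula should be corrected before any economic analysis. The reversed cost sign is certain for any strategy that adds cost, on both readings of the undefined terms. The before-after fault is the natural reading but rests on the ordinary meaning of initial and complete. On that reading, with an assumed 100 Yuan, no control cost and a 3 mmHg net effect, the planned ratio runs from -20 to -100 for control changes within 2 mmHg either way, against +33 for the quantity the plan names. The Yuan amounts and control-arm changes are assumptions that show direction and sensitivity; they do not predict the trial's result. The damage is confined to a secondary health-economic outcome, and the primary, event and safety analyses are untouched. It is a should-fix item.

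**What to change.** In SAP 5.4, with matching protocol wording, replace the three lines with:

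- IC = mean cost per participant in the intervention group minus mean cost per participant in the comparator.
- IE = the between-group SBP reduction from the primary mixed model in SAP 5.1.1, signed so that a reduction is positive (minus the intervention coefficient).
- ICER = IC / IE, separately for SS against non-SS and SSSC against non-SSSC, with an interval that respects clustering by facility.

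Using the primary model also settles which SBP value counts as final: the full-analysis set requires only one post-baseline reading, so some members will have no month-24 value.

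State how the salt is costed, since protocol V1.4 section 5.4, item 4, supplies both kinds free of charge. Valuation at market price is one option and a facility-level bootstrap is one way to get the interval; the correction does not depend on either.

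The cost is mainly wording. The point to confirm is comparator data: stock records are required of SSSC homes and supply audits of SS homes, so control-home costs may rest on central supply records. Extra potassium screening is planned only for SS participants (protocol V1.4 section 7.1), so hyperkalaemia costs will be ascertained unequally, and the report should say so.
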